**Fig 2 pone.0308413.g002:**
[figure not shown]
Auditory MMN task. (A) The auditory MMN task consists of a train of alternating tones of different frequencies, and the probability of the tones is systematically varied with a given probabilistic schedule including alternating stable and volatile phases. (B) Three-level hierarchical Gaussian filter (HGF) binary perceptual model, a Hierarchical Bayesian Model, is used to model the effect of ketamine on MMN.

### Data analysis

#### Clinical outcomes

Response will be defined as a reduction of 50% or more in the total scores of both the MADRS and GAD-7, and a 50% or greater reduction in item 10 of the MADRS scale, from baseline to the follow-up. Remission will be defined as a MADRS total score of 10 or below, assessed at the follow-up visit. C-SSRS and GAD-7 scores will be utilized to examine the association between biomedical signals and suicide and anxiety, respectively.

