## Introduction

More than 264 million people globally have depression in the context of major depressive disorder (MDD), making it the leading cause of disability worldwide [1]. Despite their common use, approximately half of patients with MDD do not respond to their first antidepressant regimen [2–4], about a third continue to be unresponsive to two or more treatment trials (i.e., treatment-resistant depression [TRD]), and it takes 4–6 weeks to discern treatment response [2]. In recent years, ketamine has attracted considerable attention for its use in MDD, including in patients with TRD. While it has been used since the 1970s as a general anesthetic [5], it has more recently been found to exert rapid antidepressant effects in people with MDD, likely via its action as a *N*-methyl-D-aspartate receptor (NMDAR) antagonist [6]. It has been shown that a subanesthetic dose of IV ketamine alleviates depressive symptoms within as little as 40 minutes of a single infusion [7], with maximum efficacy typically occurring after 24 hours [8]. Indeed, response rates of over 60% have been observed after 24 hours in patients with TRD following a single infusion of ketamine [9]. Moreover, ketamine is highly effective in reducing suicidal ideation, with this effect being largely independent from its effects on mood [10]. Although ketamine has been known to cause short-term side effects such as agitation, psychotic-like symptoms, and cognitive impairment, these side effects rarely persist more than a few hours after administration [11].

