## Methods

### Participants

This will be a single-centre study of 30 participants at St. Michael’s Hospital, Unity Health Toronto, where standard of care ketamine infusions are regularly performed in a monitored setting. Patients who are scheduled to receive ketamine treatment and are interested in participating in this study will be referred to the study coordinator. Approximately six patients are scheduled to receive IV ketamine every month. Participants aged 18 to 65 years who meet the Diagnostic and Statistical Manual for Mental Disorders (DSM-5) criteria for MDD are eligible for inclusion in the study. Participants must be in a major depressive episode at the time of screening, and have a total score of ≥10 on the Montgomery-Åsberg Depression Rating Scale (MADRS) [34]. Only those who are English-speaking and competent to consent, based on their ability to provide a spontaneous narrative description of the key elements of the study, will be included. Participants must have experienced a failure of at least two trials of antidepressant therapy during the current episode (i.e., TRD) and be receiving ketamine treatment clinically as administered by their clinician. Included participants will confirm that they are on stable doses of any concomitant psychotropic medications. If any changes to concomitant psychotropic medications are required per the patient’s standard of care, the participant will be withdrawn from the study. Patients with a history of bipolar disorder, psychosis, current diagnosis of substance use disorder or history of substance use disorder during the past year, excluding nicotine and caffeine use disorder, will be excluded from participating in this study.

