### Sample size

We expect that at least 60% of TRD patients will respond to ketamine within the first 24 hours [35]. Furthermore, power analyses under the assumption of a medium-large effect size (i.e., Cohen’s *f* = 0.4) based on previous studies [32, 36, 37] and a 15% dropout rate indicate that N = 30 participants in total will be sufficient to test our hypotheses.

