### Data collection

#### Clinical outcomes

This study will evaluate depressive symptoms, anxiety symptoms, and suicidal risk at baseline, after each ketamine infusion, and at the one-week follow-up visit. These assessments will be conducted using the MADRS, Columbia Suicide Severity Rating Scale (C-SSRS), and Generalized Anxiety Disorder 7-item (GAD-7). The MADRS [34] is a 10-item clinician-rated scale designed to measure MDD severity and detect changes due to treatment. Suicide risk will be examined using MADRS item 10 and the C-SSRS [38], a semi-structured clinical interview, which utilizes a set of prompts and questions to obtain more complete information on events suggestive of suicidality. Additionally, the GAD-7 [39] is a 7-item self-rated questionnaire designed for assessing generalized anxiety disorder.

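### The joint response rule cannot be met by a patient whose baseline MADRS item 10 (or GAD-7) is 0, because entry sets a minimum only on the MADRS total

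*Protocol article*

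**What the plan says.** In the protocol article, the Clinical outcomes paragraph under Data analysis gives the definition: "Response will be defined as a reduction of 50% or more in the total scores of both the MADRS and GAD-7", joined by a further "and" to "a 50% or greater reduction in item 10 of the MADRS scale, from baseline to the follow-up". The same paragraph defines remission on the MADRS total alone, as 10 or below at follow-up. It then assigns the C-SSRS to analyses of suicide and the GAD-7 to analyses of anxiety. Under Trial design, the follow-up visit falls about a week after the fourth infusion.

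The Participants section sets one severity minimum: patients must "have a total score of ≥10 on the Montgomery-Åsberg Depression Rating Scale (MADRS"). It asks for no minimum on the GAD-7, on item 10 or on the C-SSRS.

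The Clinical outcomes paragraph under Data collection explains what the components measure. On suicidality it says: "Suicide risk will be examined using MADRS item 10 and the C-SSRS". It describes the GAD-7 as a "7-item self-rated questionnaire designed for assessing generalized anxiety disorder". The Introduction reports that ketamine reduces suicidal ideation, "with this effect being largely independent from its effects on mood".

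The Sample size section says: "We expect that at least 60% of TRD patients will respond to ketamine within the first 24 hours".

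**The concern.** A percentage reduction needs something to reduce. The response rule requires three percentage reductions at once, but entry guarantees a positive starting value for only one of them. A patient with severe depression and no suicidal thoughts at entry meets the criteria, yet has no way to satisfy the item 10 component.

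The study aims to use model parameters for individual treatment predictions in 30 patients, and response and remission are the two categorical outcomes it defines. If the responder label depends partly on who was suicidal or anxious at entry, a parameter that tracks baseline suicidality could appear to predict treatment benefit, and a parameter that tracks mood improvement could appear not to. In a sample of 30, a handful of such patients matters. The rule also joins effects that the Introduction describes as largely separate.

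**Working it through.** **Inputs.** From the Data analysis section: the three components, the 50% threshold and the remission cut-off of 10. From Participants: the MADRS total minimum of 10 and no other severity minimum. From Sample size: 30 patients. Two inputs are assumptions: item 10 is scored 0 to 6, and a share q of patients has a baseline of 0 on item 10 or the GAD-7. The documents give neither. The main argument needs only that a score of 0 is possible.

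**The plan's own figure.** The plan gives no expected rate for this three-part endpoint, so there is nothing to reproduce. The 60% in the Sample size section refers to the first 24 hours.

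**Step 1: the item 10 component, score by score.** The condition is (baseline − follow-up) / baseline ≥ 0.5.

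- Baseline 0: no follow-up score qualifies; 0 to 0 gives 0/0, which is undefined.
- Baseline 1: only follow-up 0 qualifies.
- Baseline 2 or 3: follow-up 0 or 1.
- Baseline 4 or 5: follow-up 0 to 2.
- Baseline 6: follow-up 0 to 3.

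The argument for baseline 0 applies equally to a GAD-7 total of 0.

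**Step 2: one illustrative patient.** The MADRS total falls from 40 to 5, the GAD-7 more than halves, and item 10 is 0 throughout. The MADRS reduction is (40 − 5) / 40 = 87.5%. Since 5 is at or below 10, the patient is in remission. The item 10 component is not met, so the patient is a non-responder. One paragraph of the protocol gives both labels.

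**Step 3: sensitivity to coding.** If the condition is programmed as follow-up ≤ 0.5 × baseline, a 0-to-0 patient passes, because 0 ≤ 0. The two codings agree at every baseline from 1 to 6 and give opposite answers at 0. The text speaks of a reduction and does not provide for the second coding.

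**Step 4: effect on the response rate.** With a share q unable to meet the rule, the maximum attainable rate is 1 − q. If 60% of the others responded (a value chosen for illustration), the overall rate is 0.60 × (1 − q):

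- q = 10%: 0.60 × 0.90 = 54%, or 16.2 of 30 patients.
- q = 30%: 0.60 × 0.70 = 42%, or 12.6 of 30.
- q = 50%: 0.60 × 0.50 = 30%, or 9.0 of 30.

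**The case against.** Several points can fairly be made in the plan's defence.

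- **The sentence may be shorthand for three separate thresholds**, one for each of depression, anxiety and suicidality. The scales are introduced that way under Data collection. But the wording makes a single definition with "both" and "and", so the joint reading is the natural one. If separate outcomes were meant, the sentence still needs correcting.
- **A depression-only outcome and separate analyses already exist.** Remission uses the MADRS total alone, and the C-SSRS and GAD-7 have their own association analyses. This limits the damage but does not repair the response label.
- **A strict composite is a legitimate choice, and zero baselines are a detail that an article may leave to a fuller document.** The first part is true. On the second, the article does state a rule, and that rule gives the wrong label for an eligible type of patient. That goes beyond missing detail.

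A reader might also infer more than the documents support.

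- **That no patient with little anxiety or suicidality can respond.** This is strict only at a baseline of exactly 0. A low non-zero score can still be halved, and a GAD-7 total of 0 is a narrower case than an item 10 score of 0.
- **That the study will fall short of a planned 60% response rate, or lose a calculable amount of power.** The 60% is a 24-hour expectation. The section does not tie it to this endpoint or to the 30 patients. No responder comparison or test is specified, so no loss of power can be derived.
- **That binary response is the sole prediction target.** No section says so. The Introduction's reference to levels of therapeutic efficacy also fits a graded outcome.

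**Conclusion.** The concern holds in this form. As written, a patient with a baseline item 10 (or GAD-7) of exactly 0 cannot be a responder, whatever happens to the MADRS total, and the same patient can be in remission. With an item 10 baseline of 1, one point settles the component. This follows from the response definition and the entry criteria read together and needs no outside figure.

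The size depends on q, which the documents do not give. The ceiling on the response rate is 1 − q; the 54%, 42% and 30% figures also assume that 60% of the remaining patients respond, and are illustrations only. The 60% in the Sample size section should simply be read as a 24-hour expectation, which does not describe a three-part endpoint about a week after the last infusion.

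This should be settled before analysis. Choosing how to code a zero baseline once the data have been seen would be a post-hoc decision about who counts as a responder.

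**What to change.** Before analysis, define antidepressant response as a reduction of at least 50% in the MADRS total from baseline to follow-up. Report anxiety response (GAD-7) and antisuicidal response (item 10) as separate outcomes, each among patients with a non-zero baseline on that measure, and state how many patients that leaves.

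If the three-part composite is kept, report it as secondary, apply each component only where its baseline is above zero, and write that rule down. In the Sample size section, make clear that the 60% is a 24-hour expectation and not the expected rate for this endpoint.

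The cost is small: a dated amendment to the outcome definition while recruitment is ongoing, and smaller denominators for the anxiety and suicidality outcomes. No new data or additional patients are needed.

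### The MADRS entry floor and the remission cut-off both include 10, so an unchanged patient can be counted as a remitter, and remission partly reflects how mild the patient was at baseline

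*Protocol article*

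**What the plan says.** Three statements in the Methods of the protocol article bear on this point.

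- **Entry (Participants).** Eligible patients must "have a total score of ≥10 on the Montgomery-Åsberg Depression Rating Scale (MADRS"), and there is a separate diagnostic condition: "Participants must be in a major depressive episode at the time of screening". The score criterion applies at screening. No minimum is stated for the baseline assessment.
- **Remission (Data analysis, Clinical outcomes).** "Remission will be defined as a MADRS total score of 10 or below", judged at follow-up. This is a cut-off on the final score, with no reference to the starting score.
- **Response (same section).** "Response will be defined as a reduction of 50% or more in the total scores of both the MADRS and GAD-7", together with "a 50% or greater reduction in item 10 of the MADRS scale, from baseline to the follow-up". All three falls are required.

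Nothing in the article requires a remitter to have improved, to have responded, or to have started above 10.

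**The concern.** The same score, 10, is high enough to enrol a patient and low enough to classify that patient as remitted. A patient who does not change at all can then be counted as a treatment success. Just above that boundary, a mild entrant needs only a point or two to remit, while a severe entrant needs a large fall. The label therefore means different things for different patients.

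This matters because of what the study is for. Its stated objective is to use model parameters to make individual treatment predictions, in a prospective observational design with no comparator described. If remission is used as an outcome in that work, an EEG or model parameter that merely tracks baseline severity could appear to predict remission. No control group would show how many patients meet the cut-off without treatment.

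**Working it through.** The article gives no derived figure to reproduce here, so the check is an enumeration of the thresholds.

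**Inputs.** Screening MADRS of 10 or more (Participants). Remission if follow-up MADRS is 10 or less, and the MADRS part of response if the fall is at least 50% (both from Clinical outcomes under Data analysis). N = 30 with 15% dropout (Sample size).

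**Step 1: overlap.** The entry set (10 and above) and the remission set (10 and below) share exactly one score, 10. A patient at 10 on both occasions has a fall of (10 − 10)/10 = 0% and meets the remission rule. The entry criterion applies at screening only, so a baseline below 10 is not excluded. A patient moving from 8 at baseline to 10 at follow-up, a 25% rise, would also count.

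**Step 2: points needed, MADRS component only.** For whole-number baseline b, remission needs a fall of b − 10. The MADRS part of response needs b/2, rounded up. Before rounding, b − 10 < b/2 exactly when b < 20.

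| Baseline b | Fall to remit (b − 10) | Fall for 50% on MADRS (b/2, rounded up) | Percentage fall if follow-up is 10 |
|---|---|---|---|
| 10 | 0 | 5 | 0.0 |
| 11 | 1 | 6 | 9.1 |
| 12 | 2 | 6 | 16.7 |
| 15 | 5 | 8 | 33.3 |
| 19 | 9 | 10 | 47.4 |
| 20 | 10 | 10 | 50.0 |
| 21 | 11 | 11 | 52.4 |
| 22 | 12 | 11 | 54.5 |

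Remission is the easier target for every baseline from 10 to 19. The two are equal in whole points at 20 and 21, and remission is the harder target from 22. From 20 upward, a follow-up score of 10 or less is always a MADRS fall of at least 50%.

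**Step 3: full response definition.** Response also needs 50% falls in GAD-7 and in MADRS item 10. A patient going from MADRS 30 to 10 (a fall of 20/30 = 66.7%) with a GAD-7 fall below 50% is a remitter and not a responder. Remission without response is thus possible at any baseline. This follows from the three-part response rule and is separate from the threshold overlap.

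**Step 4: effect per patient.** Of 30 patients, one is 1/30 = 3.3 percentage points. After 15% dropout, 30 × 0.85 = 25.5, so about 25 completers, and one patient is 1/25 = 4.0 points.

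**The case against.** The strongest case on the other side has four parts.

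- **An absolute end-state and a relative change are different constructs.** A cut-off for remission need not imply any percentage fall, so its being easier than response at low baselines is not in itself an error. This stands in part. It is why a 50% fall is not proposed as the main definition. It does not excuse counting a patient with no change.
- **A reader might infer that some patients are already in remission when they enrol.** The documents do not support that. Remission is assessed only at follow-up, and every patient must be in a current major depressive episode at screening. At entry the patient meets the remission score, not a state of remission.
- **A reader might infer that remission without response is confined to baselines of 10 to 19, or is caused wholly by the overlap.** Step 3 shows otherwise. The 10 to 19 range describes the MADRS component alone.
- **The consequence is not demonstrated.** Remission is not named as the primary outcome or as the prediction target, and the sample-size paragraph refers to expected response. The baseline distribution is not given. Patients who have failed at least two antidepressant trials in the current episode and are receiving ketamine clinically may seldom score as low as 10. This stands, and it lowers the severity.

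It could also be said that covariates are left to an unseen analysis plan. That is fair for the covariate, but not for the two thresholds, which the article itself fixes.

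**Conclusion.** The point holds. Applied as written, the two inclusive limits allow a patient with an unchanged score to be counted as a remitter. For baselines of 10 to 19, remission is easier to reach than the MADRS part of response, so it partly reflects baseline severity.

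The severity is moderate. The strict overlap is a single score. The wider 10 to 19 band may hold more patients, but how many cannot be judged from the article. A reader might infer that the remission rate will be materially inflated; the documents do not support a figure for that, only the shift of 3 to 4 percentage points for each affected patient. The effect on prediction arises only if remission is modelled, which the article does not specify. The working assumes whole-number MADRS totals and either 30 analysed patients or about 25 after the stated dropout.

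**What to change.** Reconcile the Participants and Clinical outcomes sections for the analysis, before the outcome data are analysed:

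1. Count remission only among patients whose baseline MADRS is above the remission cut-off. This removes the unchanged patient at 10 and any patient whose score has dropped below 10 by baseline.
2. Include baseline MADRS, which is already collected, as a covariate in any model predicting remission. Step 1 alone leaves baselines of 11 to 19 untouched: a patient going from 11 to 10 would still remit on one point.
3. Report, as a sensitivity analysis, remission that also requires a MADRS fall of 50% or more. This would not make every remitter a responder, because GAD-7 and item 10 remain outside it, and the text should say so.

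Eligibility and data collection need not change. The cost is a few sentences, a slightly smaller denominator and possibly a lower remission rate. Because recruitment was already under way when the article was written, the change should be dated and recorded as a clarification of the outcome definition.

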#### EEG quality control and assurance procedures

Pre-processing and data quality control will be performed using established pipelines based on the Statistical Parametric Mapping toolbox (SPM12; RRID:SCR_007037) [43]. In brief, continuous EEG recordings will be referenced to the average, high-pass filtered using a Butterworth filter with cutoff frequency 0.5 Hz, down-sampled to 256 Hz, and low-pass filtered using Butterworth filter with cutoff frequency 35 Hz. The data will be epoched into 500 ms segments starting at a pre-stimulus baseline of 100 ms.

We will reject all trials overlapping with eye blink events, as detected by a thresholding routine on the vertical EOG channels, as previously used to model the effects of ketamine on sensory learning in a placebo-controlled study with healthy volunteers [44]. Finally, an artifact rejection procedure will be applied using a thresholding approach on all EEG channels to detect problematic trials or channels. Trials in which the signal recorded exceeds 75 μV relative to the pre-stimulus baseline will be removed from subsequent analysis, and channels in which more than 20% of trials need to be rejected will be marked as bad and subsequently interpolated for sensor-level statistics. Continuous ECG data will be analyzed using the same SPM12-based pipelines [43]. The ECG signal will provide information about the patient’s emotional state besides helping with removing cardiac interference on the EEG.

#### Neurocomputational mechanisms and model

Fig 3 depicts the process of analyzing the EEG signals from the MMN task. To translate the effects of ketamine on the MMN to computational mechanisms, we will model changes in the auditory MMN using the HGF [31], a Bayesian model which assumes that individuals learn not only about the probability of a stimulus, but also about the volatility of the environmental context (Fig 2B). Parameters capturing hierarchical learning during the auditory MMN task will be extracted after fitting the model to each individual’s data. These parameters will be obtained at infusion Visits 1, 2, and 4.

**Fig 3 pone.0308413.g003:**
[figure not shown]
Predicting antidepressant ketamine effects in TRD using a conductance-based neural mass model. This flowchart provides a step-by-step approach to modeling ketamine effects of perceptual inference using the auditory MMN paradigm and EEG recordings. 1) The auditory MMN, which occurs when a sequence of low tones (predictable stimulus or standard) is unexpectedly interrupted by a high tone (unpredictable stimulus or deviant). 2) The second step includes specifying the generative model, which embodies a probabilistic forward mapping from hidden brain states to observed auditory MMN. 3) The model can be inverted and applied to data for inferring underlying individual pathophysiology. (3-population neural model, with inhibitory interneuron, spiny stellate cell, and pyramidal cell populations in layer IV cortical column drawn using Adobe Illustrator). For illustration purposes, intrinsic glutamatergic connections mediated by the AMPA and NMDA receptors are grouped. 4) The utility of these models for detecting physiologically defined subgroups will be tested in TRD patients.

To link the identified computational mechanisms to their neural causes, we will apply a conductance-based neural mass model to model the cortical generators of the MMN signal [45]. Specifically, this biophysically interpretable model will allow us to investigate altered densities of specific receptor types, including NMDAR, AMPAR, and gamma-aminobutyric acid receptor (GABAR). This model assumes that cortical generators of the EEG signal can be modeled as simplified cortical columns with three neuronal populations comprising pyramidal cells, inhibitory interneurons, and spiny stellate cells. This source model rests on Morris-Lecar equations, which are extensions of the Hodgkin and Huxley’s model, scaled up for EEG analysis using the Fokker-Planck formalism [45], and parametrizes conductance properties of three different receptor types: NMDAR, AMPAR, and GABAR [30].

Electrophysiological data will be analyzed using computational models assessing disruptions in effective connectivity and NMDAR plasticity during perceptual inference [25, 33] using SPM12. This computational framework capitalizes on previous work, which has established close links between NMDAR plasticity and hierarchical precision-weighted PE learning [44, 46]. We will investigate effective connectivity and altered densities of specific receptor types (e.g. NMDAR and AMPAR) that have been implicated in pharmacological studies using MMN [47, 48].

